## **11 Data Analysis and Statistical Considerations**

### **11.1 Hypotheses**

That FBCx will be superior in cholesterol control to control group, and that Ginst15 will improve glycaemic control relative to control group.

### **11.2 Endpoints**

The primary endpoints of this study are to determine:

- The efficacy of FBCx (a formula based on  $\alpha$ -cyclodextrin (marketed under the trade name FBCx)) on cholesterol control, and
- The efficacy of Ginst15 (a ginseng extract formula based on Compound K) on glycaemic control.

### **11.3 Sample Size**

A total of 400 Participants will be recruited into the study. The study is powered for the smallest difference between two of the groups for each outcome, with the larger sample size

being adopted. This also ensures that the sample size is sufficient to determine the effect of the combination treatment (FBCx and GinST15).

FBCx (a formula based on  $\alpha$ -cyclodextrin): Assuming a mean reduction in fasting total cholesterol from baseline of 0.50 mmol/L in the intervention compared to control group, with a standard deviation (SD) of 0.90 mmol/L and an estimated drop-out rate of 15% (at 6 months), a total of 143 Participants would be required to achieve 80% power to detect a difference between the two groups (at a 2-sided significance level of 2.5%).

Ginst15 (a ginseng extract formula based on Compound K): Assuming a mean reduction in fasting plasma glucose from baseline of 0.47 mmol/L in the intervention compared to control group, with a standard deviation (SD) of 1 mmol/L and an estimated drop-out rate of 15% (at 6 months), a total of 200 Participants would be required to achieve 80% power to detect a difference between the two groups (at a 2-sided significance level of 2.5%).

Based on these calculations, 400 Participants (100 in each group) will be recruited and randomised to one of four treatment groups. All randomised Participants will be included in the final analysis.

#### **11.4 Statistical Analysis**

Data will be analysed for normality using the Shapiro-Wilk test. For analysis of differences between treatments, an analysis of covariance (ANCOVA), or the non-parametric equivalent will be used. For within group changes, repeated measures ANOVA will be used. As well as an analysis of completers (those that attend the final visit), an intention to treat (ITT) analysis will also be included. For the ITT analysis, dropouts will be treated using a variety of sensitivity analyses.

Interim analyses will be performed at end of intervention (month 6) and end of follow-up (month 12). Sub-group analyses will also be performed for those with hypercholesterolaemia, hyper-triglyceridaemia, hyper-lipidaemia and different BMI ranges.

With respect to weight loss, demonstration of a clinically significant degree of weight loss of at least 5-10% of baseline weight, which is also at least 5% greater than that associated with placebo, is considered to be a valid efficacy criterion in clinical trials evaluating new anti-obesity treatments.

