#### 6.2.11 Final Visit (Visit 12) (Month 12)

At Visit 12 (357 days after the Baseline visit +/-7), the following activities will occur:

- Urine collection (female of child bearing potential)
- Body weight
- Waist circumference
- Blood pressure and heart rate
- Blood collection
- Handgrip strength test
- Dual-energy X-ray absorptiometry (DXA) scan
- Cognitive function tests (substudy)
- Collect stool specimens (All Participants - Main Study)
- Dietitian review and collection of diet diaries
- Collection of weight record card from the self-weighing intervention group
- Completion of questionnaires
- Review and record changes to concomitant medications and dose
- AE monitoring

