## **9 Participant Completion and Discontinuation**

### **9.1 Participant Completion**

The definition of a completed Participant is if they have completed all visits according to the protocol or have met the rules in the following sections 9.2, 9.3 and 9.4.

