### **9.2 Stopping Rules / Discontinuation Criteria**

Participants can be discontinued from study treatment and assessments at any time, at the discretion of the Investigator(s). Specific reasons for discontinuing a Participant from this study are:

- Withdrawal of informed consent
- Lost to follow-up
- Pregnancy in female Participant
- Protocol non-compliance

If the Investigator considers it is not in the best interest of the Participant to continue. Even if discontinued, Investigators will aim to follow up Participants at the pre-determined time points for trial assessments unless they specifically request in writing not to be conducted.

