### **9.3 Voluntary Participant Withdrawal**

Participants are free to discontinue their participation in the study at any time, irrespective of reason. The Participant is not obliged to state his or her reason for withdrawal. However, all efforts will be made to see Participants in follow-up at pre-determined time points for trial assessments after stopping the intervention. If Participants are not willing to attend follow-up appointments then permission to maintain phone contact will be sought, unless they request in writing not to do so.

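### Section 11.4 defines completers by attendance at month 12, which does not fit the month-6 product comparison, and section 9.1 words completion in conflict with it

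*Protocol*

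**What the plan says.** Section 11.4 of the protocol names two analyses: "As well as an analysis of completers (those that attend the final visit), an intention to treat (ITT) analysis will also be included". It does not say which is primary. It adds that dropouts in the ITT analysis will be handled by a variety of sensitivity analyses, and that analyses will be run at month 6 (end of intervention) and at month 12 (end of follow-up).

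The final visit is identified in section 6.2.11 as Visit 12, month 12, day 357. Section 6.2.7 stops the supplements at Visit 8 (month 6) and at that point randomises participants again, to one of three maintenance programmes. Table 6.5.3.1 schedules fasting glucose and the lipid profile at month 6.

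The sample size in section 11.3 uses "an estimated drop-out rate of 15% (at 6 months), a total of 143 Participants would be required to achieve 80% power" for cholesterol, with the same 15% allowance at 6 months for glucose. The section ends: "All randomised Participants will be included in the final analysis".

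Section 9.1 defines a completed participant as one who is found to "have completed all visits according to the protocol or have met the rules in the following sections 9.2, 9.3 and 9.4". Section 9.2 lists discontinuation reasons, including withdrawn consent and loss to follow-up. Section 9.3 covers voluntary withdrawal: "Participants are free to discontinue their participation in the study at any time, irrespective of reason". Section 9.4 covers early termination of the study.

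**The concern.** A participant who takes product for six months, gives the month-6 blood sample and then leaves during follow-up has all the data needed to estimate the product effect at end of treatment. The rule in 11.4 removes that person from the completer analysis because of attendance in months 7 to 12. That attendance comes after product has stopped and after the second randomisation, and it may depend on how well the participant did in the first six months. If so, the completers in the arms are no longer comparable.

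There is also a practical problem. At the month-6 analysis, month-12 attendance is unknown for anyone who has not yet reached Visit 12, so the set as defined cannot be formed for them.

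Finally, the word is used in two ways. Someone lost at month 2 is completed under 9.1 and not a completer under 11.4.

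**Working it through.** **1. Reproduce the plan's sample sizes.** Inputs from section 11.3: differences 0.50 and 0.47 mmol/L, SDs 0.90 and 1.0 mmol/L, two-sided 2.5% level, 80% power, 15% drop-out at 6 months.

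Formula: n per group = 2(z₁ + z₂)²·SD²/δ², with z₁ = 2.241 and z₂ = 0.842, so (z₁ + z₂)² = 9.505.

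- Cholesterol: 2 × 9.505 × 0.81 / 0.25 = 61.6, so 62 per group, 124 in total. 124 × 1.15 = 142.6, the stated 143. (124 / 0.85 = 146.)
- Glucose: 2 × 9.505 × 1 / 0.2209 = 86.1, so 87 per group, 174 in total. 174 × 1.15 = 200.1, the stated 200. (174 / 0.85 = 205.)

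The plan's figures therefore rest on retention of 85% at month 6, not at month 12.

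**2. Power if the analysed set is month-12 attenders.** The protocol gives no 12-month retention, so every attendance figure below 85% is an assumption. Two-sample t-test, two-sided 2.5%. Pairwise means one group of 100 against another. Margins means 200 against 200 in the 2 × 2 factorial, assuming the two products do not interact.

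| Attendance | n per group, pairwise | Glucose, pairwise | Cholesterol, pairwise | Glucose, margins |
|---|---|---|---|---|
| 85% (plan, month 6) | 85 | 78.8% | 91.2% | 98.1% |
| 80% | 80 | 76.0% | 89.3% | 97.4% |
| 75% | 75 | 73.0% | 87.1% | 96.5% |
| 70% | 70 | 69.6% | 84.5% | 95.3% |
| 60% | 60 | 62.0% | 77.9% | 91.6% |

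The normal approximation gives slightly higher values (79.5% in place of 78.8% for glucose at 85 per group).

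**3. Bias if attendance depends on response.** Assumed model: month-6 glucose change normal with SD 1, mean 0 in control and −0.47 in active; logit of month-12 attendance = 1.0 − b × change, with the same rule in both arms. The mean change among attenders was computed in each arm and differenced.

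| b (log-odds per mmol/L) | Attendance, control / active | Difference among attenders | Attenuation |
|---|---|---|---|
| 0.2 | 73% / 75% | −0.466 | 0.8% |
| 0.4 | 72% / 76% | −0.457 | 3% |
| 0.8 | 71% / 77% | −0.426 | 9% |
| 1.2 | 69% / 77% | −0.391 | 17% |

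The documents do not fix b. In this model the shift is towards no effect. If the dependence differed between arms, the direction could differ too.

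**4. Set 9.1 beside 11.4.** Under 11.4 a completer is a person who attends Visit 12. Under 9.1 a person is completed either by doing all visits or by meeting 9.2, 9.3 or 9.4. Anyone who withdraws or is lost and stops attending satisfies the second and fails the first. Section 6.2.12 blurs the boundary further: the Termination visit has the same content as Visit 12 and can take place at any time after Baseline.

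**The case against.** The strongest reply is that an ITT analysis is already planned and that section 11.3 puts all randomised participants in the final analysis. A reader might infer, because completers are mentioned first, that the completer analysis is the main one and that the trial's conclusions rest on a selected set. The documents do not support that: 11.4 ranks neither analysis, and sentence order is not a hierarchy. The flaw is confined to one of two planned analyses.

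A reader might also infer that two rival completer sets will give competing efficacy results. That is not supported either. Section 9.1 concerns participant status, no analysis refers to it, and 11.4 supplies its own definition. Sections 9.2 and 9.3 also aim to keep following people who stop, so some of them may attend Visit 12. What remains is a conflict of wording.

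A third tempting reading is that the trial becomes underpowered. Pairwise glucose power does fall, and pairwise is the basis on which 11.3 was calculated. But the loss depends on assumed attendance. Pairwise cholesterol power stays above 80% down to 70% attendance, and glucose on the factorial margins stays near 92% even at 60%.

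Two further points stand. Month 6 as the primary time point is inferred from the 6-month drop-out allowance, the treatment period and the month-6 analysis; section 11.2 gives no time point. And 11.4 does not expressly apply the Visit 12 set at month 6. For month-12 outcomes, attendance at Visit 12 is an ordinary completer definition.

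**Conclusion.** The point holds in limited form. As worded, the only completer definition in the analysis section is tied to month 12. Applied literally to the month-6 product effect, it discards valid outcomes on the basis of later attendance, and it cannot be applied on time to people who have not yet reached Visit 12. The 9.1 wording contradicts 11.4 but feeds no planned analysis.

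The main harm is selection and ambiguity in a secondary or unranked analysis, not loss of power. Its size cannot be known from the protocol. At an assumed 70–75% month-12 attendance, pairwise glucose power is 69.6–73.0% against 78.8% with 85 per group, but 95.3–96.5% on the margins. Attenuation is under 1% to 17% for assumed selection log-odds of 0.2 to 1.2 per mmol/L. Certainty is high on the wording and low on the magnitude. This should be corrected before analysis; it does not threaten the trial.

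**What to change.** In section 11.4:

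- State that the ITT analysis of all randomised participants, as allocated, is primary for the two primary endpoints.
- For the month-6 analysis, define completers as participants with a month-6 (Visit 8) measurement of the endpoint, and label this a sensitivity analysis only. It is still a selection made after randomisation, so it recovers the later leavers without removing selection altogether.
- Keep the Visit 12 completer set for month-12 outcomes.

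In section 9.1, delete "or have met the rules in the following sections 9.2, 9.3 and 9.4", so that participants who meet those sections are recorded as discontinued.

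The choice of model and of missing-data methods for the ITT analysis can be left to the SAP. The cost is a few sentences in two sections and one additional analysis set, with no new data or visits.

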## **12 Data Collection and Management**

Data will be completed electronically using time and date stamped data collection tools. Questionnaires will be completed by participants on a platform called Qualtrics and source data will be entered directly by investigators at the time of each visit into OpenClinica. Paper food diaries will be collected and entered by participants on an electronic platform. Each of the platforms and the OpenClinica database will be password protected and backed up on The University of Sydney server.

Data collected from the “Australian Type 2 Diabetes Risk Screening Assessment Tool” (Appendix R) will be stored in a secured database (Oracle) which will be backed up on a daily basis on CPU and disc resources.

## **13 Monitoring and Quality Assurance**

The task of the Sponsor is to guarantee the best conduct of the study through frequent contacts by phone and in person with the responsible Investigator with the purpose of facilitating the work and fulfilling the objectives of the study. These site visits will enable the Sponsor to maintain current, personal knowledge of the study through review of the records, comparison with source documents, and observation and discussion of the conduct of the study with the Investigator. The Sponsor is responsible for monitoring adherence to the Protocol and completion of the eCRF, and for the relationship between the Investigator and Sponsor.

In order to ensure the accuracy of data, direct access to source documents by representatives of the Sponsor and regulatory authorities is mandatory. Anonymity of the Participant will be maintained at all times. The Sponsor reserves the right to terminate the conduct of the study at any particular site for refusal of the Investigator/Institution to supply source documentation of work performed in the study.

### **13.1 Curriculum Vitae and Other Documentation**

The present investigation may constitute a part of a national registration file. In order to comply with regulatory requirements in some countries, all Investigators signing the Protocol and all trial staff should provide a current, signed and dated Curriculum Vitae (CV) to be filed by the Sponsor. The CV should include name, title, occupation, education, research experience and present and former positions, be signed and dated every two years. A Staff

Signature List or delegation log is required. Principal Investigators may also be requested to complete a financial disclosure form.

## **14 Investigator Responsibility**

Except where the Principal Investigator's signature is specifically required, it is understood that the term 'Investigator' as used in this Protocol and on the eCRF refers to the PI or an appropriately qualified member of the staff that the PI designates to perform specified duties of the Protocol as delegated on the Staff Signature List or delegation log. The PI is ultimately responsible for the conduct of all aspects of the study.

Each Investigator will comply with the local regulations and guidelines regarding the conduct of clinical trials and the Investigator responsibilities, including but not limited to, the International Conference on Harmonisation (ICH) GCP guidelines, as adopted by the Therapeutic Goods Administration (TGA).

## **15 Study Report**

The final study report will be based on ICH Harmonised Tripartite guidelines E3.

<http://www.ich.org/products/guidelines/efficacy/efficacy-single/article/structure-and-content-of-clinical-study-reports.html>

## **16 Administrative Procedures**

### **16.1 Ethical Considerations**

Information on side effects of the test and reference formulations is summarised in the Investigator's Brochure or product insert. The monitoring and safety guidelines are outlined in the Monitoring Guidelines for the study. The amount of blood to be sampled in the study is not considered to be excessive in healthy adult Participants. This study will be carried out according to the principals of the Declaration of Helsinki, the National Health and Medical Research Council (NHMRC) National Statement on Ethical Conduct in Research Involving Humans and the Notes for Guidance on Good Clinical Practice as adopted by the Australian Therapeutic Goods Administration (2000) (CPMP/ICH/135/95) (GCP). These documents are available on the internet and will not be annexed to this Protocol.

## **16.2 Ethical Review Committee**

The Protocol will be submitted for approval to the Sydney Local Health District HREC (Royal Prince Alfred Hospital), and written approval obtained, before volunteers are recruited and Participants are enrolled. The Investigators will receive all the documentation needed for submitting the present Protocol to the HREC. A copy of the respective approval letters will be transmitted to the Sponsor before starting the study. The composition of the HREC will also be provided to the Sponsor. If approval is suspended or terminated by the HREC, the Investigator will notify the Sponsor immediately.

It is the responsibility of the Investigator to report study progress to the HREC as required or at intervals not greater than one year.

The PI, or their nominee, will be responsible for reporting any serious adverse events to the HREC as soon as possible, and in accordance with the guidelines of the HREC.

The final study Protocol, including the final version of the Information for Participants, must be approved in writing by the Sydney Local Health District HREC (Royal Prince Alfred Hospital).

The PI is responsible for informing the HREC of any amendment to the Protocol. In addition, the HREC must approve all advertising used for recruitment for the study.

The PI must submit progress reports to the HREC as required.

## **16.3 Regulatory Authorities**

This study will be notified to the Therapeutic Goods Administration (TGA) under the Clinical Trial Notification (CTN) scheme.

Any specific SAEs will be reported to the Sponsor as detailed in this Protocol. In agreeing to the provisions of the Protocol, these responsibilities are accepted by the Investigator.

## **16.4 Informed Consent**

The PI, or a person designated by the PI on the delegation of responsibility sheet, should ensure that the Participant is given full and adequate oral and written information about the nature, purpose and possible risks and benefits of the study.

Participants must also be notified that they are free to discontinue the study at any time. The Participant should be given the opportunity to ask questions and should be allowed time to consider the information provided.

The Participant's signed and dated informed consent must be obtained before conducting any procedure specifically for the study. The consent forms shall be signed and dated by the appropriate parties.

A copy of the Participant Consent Form must be given to the Participant at the time of signing the document. A notation that written informed consent has been obtained will be made on the Participant's case notes. The completed consent forms will be retained by the Investigator for review by the Sponsor.

### **16.5 Participant Reimbursement**

Participants will be given a \$20.00 AUD food debit card at each study visit from Baseline through to Month 12. The food debit card works at many of the major supermarket chains and is encrypted to allow the purchase of food only.

If the study is terminated by Sponsor or the Investigator prior to completion or a Participant withdraws or is withdrawn from the study before completion, a pro-rata payment will be made at the discretion of the Investigator(s).

### **16.6 Emergency Contact with Investigators**

All Participants will be provided with a Participant Emergency Contact Card (approved by the HREC) with contact details of whom to contact in the case of an emergency.

### **16.7 Notification of Primary Care Physician**

There is no requirement for the PI to notify the primary care physician of the Participant's participation in the study.

### **16.8 Investigator Indemnification**

The study is being conducted in accordance with the 'Guidelines for Compensation for Injury Resulting from Participation in a Company-Sponsored Clinical Trial' published by the Medicines Australia. The Sponsor will reimburse Participants for costs of medical care that occur as a result of complications directly related to participation in this study.

### **16.9 Payments**

Any payments related to the conduct of the study are subject to a formal agreement between the Sponsor and the Investigator or Institution.

## **16.10 Protocol Amendments**

No changes (amendments) to the Protocol may be implemented without prior approval from the Sponsor.

Changes and amendments to the Protocol can only be made by the Sponsor. Approval of amendments by the Institutional HREC is required prior to their implementation. In some instances, an amendment may require a change to a consent form. The Investigator must receive approval/advice of the revised consent form prior to implementation of the change. In addition, changes to the data collected, if required, will be incorporated in the amendment. The Investigator should not implement any changes to, or deviations from, the Protocol except where necessary to eliminate immediate hazard(s) to Participants.

It is the responsibility of the Investigator to submit the amendment to the HREC for their approval; written approval should be obtained and a copy provided to the Sponsor. The Sponsor is responsible for determining whether or not the local regulatory authority must be notified of the Protocol change. Completed and signed Protocol amendments will be circulated to all those who were on the circulation list for the original Protocol.

The original signed copy of amendments will be kept in the Investigator File with the original Protocol. It should be noted that where an amendment to the Protocol substantially alters the study design or the potential risks to the Participants, each Participant's consent to continue Participation should be obtained.

